### 160 3.6 Research Plan

- 161 ● Patients were recruited by subject recruitment advertisements and sleep clinics, interviewed in  
162 person, screened after signing informed consent, and demographic data, medical history, and  
163 clinical information were collected on the day of screening.
- 164 ● Those who met the inclusion criteria were randomly assigned to the group after recording a  
165 sleep diary for at least 3 days.
- 166 ● A bracelet was issued on the day of enrollment, instructions were given to download the app,  
167 and access to the appropriate group was logged in based on the randomization number. A  
168 6-week period of dCBT-I or sleep education was started on the day of enrollment, and  
169 compliance and efficacy were monitored by investigators without intervention.
- 170 ● Follow-up schedule(online/offline): at the end of the intervention, 1 month, 3 months, and 6  
171 months after the end of the intervention.
- 172 ● Study endpoint: 6 months after the end of the intervention.
- 173 ● Clinical information related to study indicators included: symptoms, physical examination and  
174 medication information, scale assessments (ISI, DBAS-16, FSS, SF-12, GAD-7, PHQ-9), sleep  
175 diary, and bracelet recording of sleep indicators. The time points for collection were: baseline,  
176 at the end of the intervention, 1 month, 3 months and 6 months after the end of the  
177 intervention.
- 178 ● Follow-up continued for 6 months after the end of the study (1 year after the end of the  
179 intervention) and subjects who volunteered to participate completed symptoms online scale  
180 assessments (ISI, DBAS-16, FSS, SF-12, GAD-7, PHQ-9) and recorded a 1-week sleep diary.

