### 145 3.5 Research Indicators

146 3.5.1 Primary endpoint indicator: insomnia severity index (ISI)

147 3.5.2 Other study metrics:

- 148 ● Online sleep diary (7d): total time in bed (TIB), total sleep time (TST), sleep efficiency (SE),  
149 and total time awake (TWT) were calculated from the sleep diary
- 150 ● Smart bracelet recorded: total sleep time, number of times waking up during sleep, wake up  
151 time and sleep quality.
- 152 ● Simplified Sleep Attitudes and Beliefs Questionnaire (DBAS-16)
- 153 ● Fatigue Severity Scale (FSS)
- 154 ● Quality of Life Questionnaire (SF-12)
- 155 ● Generalized Anxiety Disorder Assessment (GAD-7)
- 156 ● Patient Health Questionnaire (PHQ-9 Depression Screening)

157 3.5.3 Other information to be collected: age, sex, education, employment status, living and residence  
158 status, demographic data, current medical history, past medical history and medication, smoking and  
159 alcohol consumption, body mass index (BMI), etc., and adverse effects during treatment.

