### 192 3.8 Data Management

- 193 ● Data collection: Data collection: Primary and secondary outcomes at baseline and follow-up  
194 were completed by the investigator at the in-person visit. Subjects' sleep diaries recorded via  
195 the App. The App data and bracelet data were exported by technical support staff and stored at  
196 the Department of Respiratory and Critical Care Medicine in Peking University First Hospital.  
197 To ensure the completeness and accuracy of the survey data, all data were verified and  
198 accepted prior to entry.
- 199 ● Entry and preservation: All original data can be entered only after de-identifying information,  
200 and will be summarized and preserved by the Department of Respiratory and Critical Care  
201 Medicine, Peking University First Hospital.
- 202 ● Quality control and verification of data management: clinical data are entered into the database  
203 synchronously and independently in double copies. Random sampling of data is performed by  
204 data management staff. Lock the database after comparing with no errors.  
205

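### The schedule asks for a baseline bracelet recording but hands out the bracelet on the day treatment starts, so no pre-treatment bracelet night exists; the diary baseline is guaranteed only 3 of its 7 days

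*Protocol*

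**What the plan says.** Section 3.6 of the protocol sets the order of events. Screening follows consent. Then: "Those who met the inclusion criteria were randomly assigned to the group after recording a" "sleep diary for at least 3 days". Next: "A bracelet was issued on the day of enrollment, instructions were given to download the app". Log-in to the assigned arm of the App uses the randomisation number. On the start of treatment the section says: "6-week period of dCBT-I or sleep education was started on the day of enrollment, and" goes on to describe monitoring.

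The same section then lists what is collected and when, including: "diary, and bracelet recording of sleep indicators. The time points for collection were: baseline", followed by the end of the intervention and 1, 3 and 6 months after it.

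Section 3.5.2 defines the measures. For the bracelet: "Smart bracelet recorded: total sleep time, number of times waking up during sleep, wake up" time, and sleep quality. For the diary: "Online sleep diary (7d): total time in bed (TIB), total sleep time (TST), sleep efficiency (SE") and time awake. Section 3.8 adds: "Subjects' sleep diaries recorded via" the App, with no exception for the run-in.

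**The concern.** A baseline has to be measured before treatment can act, and preferably before allocation is known. Section 3.6 requires a bracelet baseline but puts the first possible night of wear after randomisation and on or after the day treatment begins. Section I calls the trial open, so participants would also know their arm while that baseline was being recorded.

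Early effects are plausible on the protocol's own account. Section I reports that 85% of patients improved in subjective sleep quality within two weeks. Section 3.4 includes sleep restriction, and section IV accepts that this could in theory cause sleep deprivation. An early effect on bracelet sleep time could therefore go in either direction.

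At stake is any bracelet analysis that uses a baseline, whether as a change score, as a covariate, or as the first time point in the mixed models of section 3.9. The bracelet is the only device-recorded sleep measure in the trial.

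The diary raises a smaller question. The run-in minimum is shorter than the outcome window, and the App in which diaries are kept is not mentioned until enrolment.

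**Working it through.** **Plan's own figures.** The protocol gives no figure for this point. The sample size in section 3.7 rests on the ISI alone (difference 6, SD 8, two-sided 0.05, power 80%). A two-sample t-test gives 28.9, so 29 per group with power 0.801, as stated. Nothing below changes it.

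**Step 1: order of events for the bracelet (section 3.6).**

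| Order | Event | Bracelet worn? |
|---|---|---|
| 1 | Consent and screening | No |
| 2 | Diary run-in, 3 days or more | No, not yet issued |
| 3 | Randomisation | No |
| 4 | Day of enrolment: bracelet issued, App log-in by randomisation number, intervention starts | First possible night |

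Scheduled bracelet nights before treatment: 0. This does not depend on how enrolment is read, because issue and treatment start share the same day. The log-in by randomisation number shows that this day is at or after allocation.

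**Step 2: effect on the analysis.** Let d0 be the expected between-arm difference in a bracelet measure during the nights taken as baseline, d1 the difference at follow-up, and b the slope on baseline in an adjusted analysis.

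- Follow-up values only: estimate = d1.
- Change from baseline: estimate = d1 − d0.
- Baseline-adjusted: estimate = d1 − b·d0.

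With a pre-randomisation baseline, d0 = 0 in expectation and all three agree. With an on-treatment baseline, d0 need not be 0. If d0 has the sign of d1, the effect is understated; if it has the opposite sign, the effect is overstated. The protocol gives nothing from which to estimate d0, so the bias has no number.

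**Step 3: diary days guaranteed.** The run-in minimum is 3 days (section 3.6) and the outcome window is 7 days (section 3.5.2): 3/7 = 43%. Seven or more are permitted but not required.

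**Step 4: what 3 nights rather than 7 could cost.** The protocol gives no night-to-night correlation, so a single-night intraclass correlation (ICC) of 0.2 to 0.6 is assumed, purely as illustration.

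- Reliability of a k-night mean: k·ICC / (1 + (k − 1)·ICC).
- Variance of a k-night mean, relative to single-night variance: ICC + (1 − ICC)/k.

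| Assumed ICC | Reliability, 3 nights | Reliability, 7 nights | Variance ratio, 3 to 7 nights |
|---|---|---|---|
| 0.2 | 0.43 | 0.64 | 1.49 |
| 0.3 | 0.56 | 0.75 | 1.33 |
| 0.4 | 0.67 | 0.82 | 1.24 |
| 0.5 | 0.75 | 0.88 | 1.17 |
| 0.6 | 0.82 | 0.91 | 1.12 |

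Worked line for ICC 0.2: variance is 0.2 + 0.8/3 = 0.467 for 3 nights and 0.2 + 0.8/7 = 0.314 for 7, a ratio of 1.49. These figures are for a participant who records only the minimum.

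**Step 5: diary route.** Section 3.8 has diaries recorded in the App, and section 3.5.2 calls the diary online. Section 3.6 first mentions downloading the App on the day of enrolment, after the run-in diary is complete. No section says how the run-in diary is kept.

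**The case against.** The strongest reply is that little depends on this. The primary endpoint is the ISI, a questionnaire that needs neither device nor diary. The bracelet is listed among the other study metrics, and the protocol nowhere defines its outcome as change from baseline. Randomisation supports a direct comparison of bracelet values at each follow-up. The App delivers its content step by step over weeks, so the effect on the first few nights may be small. All of this stands. It limits the consequence, but it does not remove the conflict between a listed baseline and a device not yet issued. A statistical analysis plan can define a window but cannot supply nights that were never recorded.

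On the diary, a reader might infer three stronger things that the documents do not support:

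- **That no valid diary baseline can be obtained.** A diary of at least 3 days before randomisation is required of everyone, and the wording allows 7.
- **That the run-in diary is kept in a different medium.** The protocol does not say so; the route is unstated and sits awkwardly with section 3.8.
- **That the mismatch biases the treatment comparison.** A shorter or differently recorded pre-randomisation baseline applies to both arms alike. It adds noise and makes within-arm change harder to interpret, but leaves the between-arm contrast unbiased.

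**Conclusion.** The bracelet point holds. Section 3.6 schedules a baseline recording that its own order of events rules out: zero pre-treatment nights for every participant. Bracelet analyses that use such a baseline would be biased to the extent that treatment, or knowing one's arm, alters the first nights. The size and direction of that bias cannot be derived from the protocol. It would be wrong to conclude that the bracelet data are unusable or that the trial's main result is at risk: follow-up-only comparisons, the ISI endpoint and the sample size are untouched.

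The diary point holds in a limited form. Only 43% of the defined window is guaranteed before randomisation, and the recording route needs to be stated. At the 3-day minimum, the variance of the baseline mean would be about 1.1 to 1.5 times that of a 7-night mean, on the assumed ICC range of 0.6 down to 0.2. This is a loss of precision and comparability, not a bias between arms.

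Overall this is a correction worth making before enrolment, of moderate weight because only secondary measures are involved.

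**What to change.** Reconcile sections 3.5.2, 3.6 and 3.8 as follows:

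1. At screening, after consent, issue the bracelet and a diary-only App login.
2. Record both during the existing run-in, extended to 7 nights to match section 3.5.2.
3. Unlock the allocated App content only after randomisation.
4. Define baseline for both measures as those pre-randomisation nights.

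The cost is up to 7 − 3 = 4 more run-in days for a participant who would have recorded only the minimum, a diary-only access mode in the App, and some bracelets lent to people who are then not randomised. Screening is already in person, so no further assessment is needed.

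If the schedule cannot change, remove baseline from the bracelet collection times and compare bracelet follow-up values between arms without a bracelet baseline. That costs nothing in logistics but gives up the precision a valid baseline would bring. The diary route and baseline window should be stated in either case.

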### 183 3.7 Sample size

184 This was a randomized controlled study with a parallel design, with the intervention group being  
185 the dCBT-I treatment group and the control group being the general sleep education group, with a  
186 sample size of 1:1 in both groups. using the Insomnia Severity Index (ISI) as the main study index, the  
187 difference in ISI improvement after treatment was estimated to be approximately 6 with a standard

188 deviation of approximately 8, based on previous literature, set at  $\alpha=0.05$  (two-sided test), with a  
189 certainty of  $1-\beta=80\%$ . The sample size of 29 cases per group was calculated using PASS 11.0 software.  
190 Based on the assumption of a 30% shedding rate reported in previous studies, a total sample size of  
191  $n=2*(29/0.7) \approx 82$  cases is required, with 41 cases of study subjects included in each group.

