In recent years, with the popularization of information technology, Internet-based CBT-I has been established and developed to provide convenient, standardized and homogeneous treatment services for insomnia patients, breaking through the limitations of time and space. Networked CBT-I is mainly

divided into two forms: full/partial participation of therapists and full self-help without therapist participation. Full self-help is the most economical way, but it requires high technical requirements and poor compliance. Several RCT studies and meta-analyses have been conducted abroadxvii, xviii show , internet CBT-I can significantly reduce the severity of insomnia, improve sleep efficiency and total sleep time, enhance sleep confidence, and reduce the occurrence of depression compared with the waiting treatment group or the general sleep education group. internet CBT-I has shown its unique advantages and attracted high attention since the global novel coronavirus outbreak in the first half of 2020. Internet CBT-I in China is still in its infancy, and existing ongoing registration studies use a networked CBT-I system with psychoeducation and homework as the main interventions, with the goal of reducing the occurrence of depression and reducing the formation of related suicidal ideation in insomniacs.

The main problems with current networked CBT-I are: 1. Internet-based CBT-I in most clinical studies is implemented through a web-based platform, and there are relatively few digital CBT-I (dCBT-I) implemented using mobile device applications, which are simpler to implement, more flexible, and have a wider audience, and may be more suitable for the reality of our country where economic and cultural development is uneven but smartphones are very popular. 2. poor adherence to fully self-help CBT-I treatment in clinical studies, with a shedding rate of about 20%-45%, may be related to the fact that the software implements education through reading or video but has insufficient interactive features. 3. most web-based CBT-I implementations follow a set sequence of modules one by one, with insufficient individualization of patient response to treatment, which affects efficacy and time to achieve efficacy.

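### Section 3.7 rounds 82.86 down to 82, so 41 per arm at 30% loss leaves an expected 28.7 evaluable, just under the required 29 (power 79.7%, not 80.1%)

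*Protocol*

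**What the plan says.** Section 3.7 (Sample size) of the protocol sizes the trial on the Insomnia Severity Index (ISI).

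- **Effect and spread:** the "difference in ISI improvement after treatment was estimated to be approximately 6", with a standard "deviation of approximately 8, based on previous literature".
- **Error rates and allocation:** alpha 0.05 ("two-sided test"), power 80%, and a "sample size of 1:1 in both groups".
- **Evaluable number:** "The sample size of 29 cases per group was calculated using PASS 11.0 software".
- **Allowance for loss:** "Based on the assumption of a 30% shedding rate reported in previous studies, a total sample size of" 2*(29/0.7), which is printed as approximately 82, "cases is required, with 41 cases of study subjects included in each group".

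Section I (Research Overview / Background / Rationale) describes fully self-help CBT-I in clinical studies "with a shedding rate of about 20%-45" percent. Section 3.9 (Statistical Analysis) names t-tests or rank sum tests for continuous variables, mixed regression models for longitudinal data, and an intention-to-treat analysis of the primary outcome.

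**The concern.** The equation is printed in full, so it can be checked directly, and its two sides do not agree. The left side is 82.86. Ordinary rounding gives 83, and rounding a minimum up to whole, equal arms gives 84. Only truncation gives 82.

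The direction matters in principle because 29 is the smallest whole number per arm that reaches 80% power under the stated inputs, so there is almost no slack to absorb rounding down. The protocol calls 82 the required number, yet at the loss rate it assumes, 82 does not deliver the 29 per arm that it derived one sentence before. What is at stake is the accuracy of a stated design figure, and very little power.

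**Working it through.** **Inputs, all from section 3.7:** difference 6, SD 8 (standardised difference d = 6/8 = 0.75), two-sided alpha 0.05, power 80%, allocation 1:1, loss 30%.

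**Step 1: reproduce the 29.** Solving the two-sample t-test power equation (noncentral t) for n at d = 0.75 gives 28.90 per arm, which rounds up to 29. Power at 29 per arm is 80.1%. The plan's figure is reproduced. The normal approximation would give 28, so the t-test version is the one that matches the stated 29.

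**Step 2: inflate for loss.** The form n/(1 - loss) is correct.

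- Per arm: 29/0.7 = 41.43, rounded up to 42.
- Total: 2 x 29/0.7 = 82.86. Whole, equal arms need 2 x 42 = 84.
- Stated: 82 in total, 41 per arm.

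**Step 3: work back from the enrolled number at 30% loss.**

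| Enrolled per arm | Expected evaluable per arm | t-test power |
|---|---|---|
| 41 (stated) | 41 x 0.7 = 28.7 | 79.7% |
| 42 (rounded up) | 42 x 0.7 = 29.4 | 80.7% |
| Requirement | 29 | 80.1% |

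The shortfall is 29 - 28.7 = 0.3 of a patient per arm, and the cost is 80.1 - 79.7 = 0.4 percentage points. In whole patients, 82 x 0.7 = 57.4. With 57 completers split 28 and 29, power is 79.4%. With only 28 in each arm it is 78.7%, but that rounds down twice and overstates the expected shortfall. The largest loss at which 41 per arm still leaves 29 is 1 - 29/41 = 29.3%.

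**Step 4: scale against the precision of the inputs.** The difference and SD are both given as approximate. With 29 per arm, an SD of 8.05 instead of 8 already gives 79.7%, and an SD of 8.5 gives 75.2%. The rounding is smaller than the precision that the protocol claims for its inputs.

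**Step 5: optional sensitivity to loss, 41 per arm, completers-only t-test.** Applying any of these rates to this trial is an assumption.

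| Loss, app arm / control arm | Expected evaluable | Power |
|---|---|---|
| 20% / 20% | 32.8 / 32.8 | 84.9% |
| 30% / 30% | 28.7 / 28.7 | 79.7% |
| 45% / 30% | 22.55 / 28.7 | 74.3% |
| 45% / 45% | 22.55 / 22.55 | 69.2% |

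**The case against.** **The slip is immaterial.** The total is printed with an approximation sign, the inputs are approximate, and the loss in power is 0.4 points. This stands as a judgement of size. It does not make the equation correct: no usual rounding rule takes 82.86 to 82, and the result is stated as a required number.

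**A reader might infer more: that the plan ignores its own 20%-45% loss range and is therefore badly underpowered.** The documents do not support this, for four reasons.

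- The 30% lies inside that range, close to its midpoint of 32.5%, and section 3.7 attributes it to previous studies. Taking one planning value from within a range is ordinary practice and contradicts nothing.
- Section I gives the range for fully self-help CBT-I and suggests that it may be linked to software with too little interaction. The control arm receives sleep hygiene and stimulus control education (section 3.4), and section I presents the interactive app as a possible way to improve adherence. The protocol does not say that 45% applies to this app, still less to both arms.
- The 69.2% figure needs 45% loss in both arms. With 45% in the app arm and 30% in the control arm, power is 74.3%.
- All these figures assume a completers-only t-test. Section 3.9 names mixed models and intention-to-treat, and a patient who stops using the app may still supply an ISI score, so some of the information could be recovered.

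It remains true that the protocol gives no reason for choosing 30% within the range and no power at other loss rates. That is a gap which a sensitivity calculation could fill, and not an error. Enrolling 84 would not address it either: with 45% loss in both arms, 42 per arm leaves 23.1 and power is 70.3%.

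**Conclusion.** The point holds as a minor arithmetic correction. The printed equation is wrong: 2*(29/0.7) is 82.86, and 41 per arm at the stated 30% loss leaves an expected 28.7 evaluable per arm against a requirement of 29. Power is 79.7% instead of 80.1%, assuming a two-sided t-test on completers with difference 6, SD 8 and equal 30% loss in both arms. The derivation of 29 and the form of the inflation are both right. The slip does not threaten the trial, and the 30% loss assumption is not shown to be wrong.

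**What to change.** Change one sentence in section 3.7, in either of two ways.

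- **Correct the number:** 29/0.7 = 41.43, rounded up to 42 per group, 2 x 42 = 84 in total. This costs two more patients.
- **Keep 82 and restate what it delivers:** 41 per group, about 28.7 evaluable per arm, power approximately 79.7% at 30% loss (unadjusted t-test). This costs no patients.

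Optionally, add one line of sensitivity: under a completers-only t-test with 41 per arm, power would be about 74% if 45% were lost in the app arm and 30% in the control arm, and about 69% if 45% were lost in both. Label those loss rates as assumptions.

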### 192 3.8 Data Management

- 193 ● Data collection: Data collection: Primary and secondary outcomes at baseline and follow-up  
194 were completed by the investigator at the in-person visit. Subjects' sleep diaries recorded via  
195 the App. The App data and bracelet data were exported by technical support staff and stored at  
196 the Department of Respiratory and Critical Care Medicine in Peking University First Hospital.  
197 To ensure the completeness and accuracy of the survey data, all data were verified and  
198 accepted prior to entry.
- 199 ● Entry and preservation: All original data can be entered only after de-identifying information,  
200 and will be summarized and preserved by the Department of Respiratory and Critical Care  
201 Medicine, Peking University First Hospital.
- 202 ● Quality control and verification of data management: clinical data are entered into the database  
203 synchronously and independently in double copies. Random sampling of data is performed by  
204 data management staff. Lock the database after comparing with no errors.  
205

